## Abstract

**Background:**

Knee osteoarthritis is the most common type of arthritis, with pain being its most common symptom. Little is known about the psychological aspects of knee osteoarthritis pain. There is an emerging consensus among osteoarthritis specialists about the importance of addressing not only biological but also psychosocial factors in the assessment and treatment of osteoarthritis. As few studies have evaluated the effect of psychological interventions on knee osteoarthritis pain, good quality randomized controlled trials are needed to determine their effectiveness.

**Methods/Design:**

We intend to conduct a 6-week single-blinded randomized controlled trial with a 12-month follow-up. Altogether, 108 patients aged from 35 to 75 years with clinical symptoms and radiographic grading (KL 2–4) of knee osteoarthritis will be included. The clinical inclusion criteria are pain within the last year in or around the knee occurring on most days for at least one month, and knee pain of ≥40 mm on a 100-mm visual analogue scale in the WOMAC pain subscale for one week prior to study entry. Patients with any severe psychiatric disorder, other back or lower limb pain symptoms more aggravating than knee pain, or previous or planned lower extremity joint surgery will be excluded. The patients will be randomly assigned to a combined GP care and cognitive-behavioral intervention group (n = 54) or to a GP care control group (n = 54). The cognitive-behavioral intervention will consist of 6 weekly group sessions supervised by a psychologist and a physiotherapist experienced in the treatment of pain. The main goals of the intervention are to reduce maladaptive pain coping and to increase the self-management of pain and disability. The follow-up-points will be arranged at 3 and 12 months. The primary outcome measure will be the WOMAC pain subscale. Secondary outcome measures will include self-reports of pain and physical function, a health related quality of life questionnaire, and various psychological questionnaires. Personnel responsible of the data analysis will be blinded.

**Discussion:**

This study addresses the current topic of non-pharmacological conservative treatment of knee OA-related pain. We anticipate that these results will provide important new insights to the current care recommendations.

**Trial registration:**

Current Controlled Trials ISRCTN64794760

## Background

Osteoarthritis (OA) is the most common form of arthritis and a major contributor to functional disability [1]. It represents a major social and health problem in the elderly, imposing an increasingly heavy economic burden on social welfare and health care systems. This is due to the need for surgical and medical interventions and frequent absenteeism from work [2]. Although not all OA is symptomatic, the World Health Organization has estimated that OA is the cause of disability in at least 10% of the population over the age of 60 years [3].

Knee OA is the most common type of arthritis. The main symptom of knee OA is pain, which is generally related to joint use and relieved by rest. However, the association between radiological changes in knee OA and the severity of pain or the level of disability is not straightforward. As OA progresses, the pain may become more persistent and also manifest itself at rest. In addition to pain, loss of function and joint stiffness are typical symptoms of OA, which often lead to difficulties in performing daily activities.

The assessment and treatment of pain is vital to the management of OA [4]. It is known that chronic pain is associated with increased considerable psychological distress, such as anxiety and depression. One population study from 17 different countries found that depression and anxiety disorders occurred significantly more often in individuals with self-reported arthritis, with depression present in 5−10% of those with arthritis [5]. In another study conducted by Smith and Zautra, measures of anxiety and depression emerged as independent and significant predictors of current and future pain [6].

The cognitive-behavioral (CB) perspective presented by Turk et al. [7] is the most widely accepted model in the field of pain psychology. It has led to the identification of cognitive and other psychological factors that are associated with pain severity and disability. If one considers the constructs that have the strongest empirical support, factors like pain catastrophizing [8], fear-avoidance [9], self-efficacy and lack of perceived control [10,11], and passive pain coping [12] have been claimed to be of importance. Factors, such as pain catastrophizing and pain-related fear, have been found to be strongly and consistently associated with pain severity and disability in patients with musculoskeletal pain [13] and knee OA [4]. Low self-efficacy and helplessness have also been identified as predictors of disability in OA patients [14,15].

According to several reviews, psychological factors influence not only pain and disability, but also in particular the transition from the presence of acute to chronic pain [13,16]. However, there have been relatively few attempts to prevent chronic disability in OA by adopting a CB approach. Calfas et al. conducted a randomized controlled trial (RCT) testing a 10-week group-based CB program on 40 OA patients [17]. They concluded that in the long term, physical and psychological functioning did not differ between the CB and the education control group. In 2011, Riddle et al. published the results of a quasi-experimental study testing an 8-session individual pain coping skills training (PCST) program in patients with elevated pain catastrophizing who were scheduled for knee arthroplasty [18]. They found that the PCST program resulted in significantly greater reductions in pain severity and catastrophizing, and greater improvements in function when compared with the usual care cohort. Somers et al. recently reported the results of an RCT studying the effects of a PCST program and a behavioral weight management intervention [19]. They concluded that the combination of these two treatments yielded significantly better outcomes in terms of pain, physical disability, stiffness, activity, arthritis self-efficacy, and weight self-efficacy than either of the intervention modalities alone or that evident in the control group.

There are several trials that have used behavioral interventions with similarities to CB principles as well as studies that have integrated CB principles with other forms of rehabilitation in OA patients. For example, Hurley et al. conducted an RCT assessing the effects of a combined exercise, self-management, and active coping strategies rehabilitation program [20]. They found over the long-term, that the rehabilitated participants enjoyed better physical function, lower community-based health care costs, medication costs, and total health and social care costs as well as concluding that there was a high probability (80–100%) that the program was cost effective. On the other hand, Keefe et al., adopted an RCT setting to investigate the separate and combined effects of spouse-assisted pain coping skills training and exercise training in patients having persistent osteoarthritic knee pain [21]. They concluded that the kind of intervention combining spouse-assisted coping skills training and exercise training could improve physical fitness, strength, pain coping, and self-efficacy in patients suffering from pain due to OA.

One CB-based approach in treating pain-related disability and chronicity is the 6-session group intervention model presented by Linton [22]. The model was originally developed for early identification and intervention in the prevention of musculoskeletal pain [23,24]. The standardized 6-session program focused on coping, function and cognitions and the application of learning principles to allow the individual to utilize more adaptive methods of pain management and active coping [22]. The model has previously been tested in RCT setting in patients with back and neck pain [23-25]. In these studies, the CB intervention led to less short- and long-term work absenteeism, fewer health care visits, decreased perceived risk and fear-avoidance beliefs, and a larger number of pain-free days.

The present study aims to explore the effectiveness and cost-effectiveness of the CB group intervention described by Linton [22], modified for patients with knee OA. As far as we are aware, there have been no previous studies using this approach in patients with knee OA. The working hypothesis is that patients with symptomatic knee OA will benefit from this kind of CB rehabilitation program. More specifically, we intend to examine the effect of the intervention in terms of self-reported physical function and pain, pain-related work abstinence, the number of pain-related health care visits, and health-related quality of life (HRQoL). We also aim to determine the effect of the intervention on several psychological variables such as depression, anxiety, sense of coherence, pain catastrophizing, kinesiophobia, self-efficacy, and life satisfaction. Finally, we plan to run a cost-utility analysis of the intervention based on quality-adjusted life years (QALY).

## Methods/Design

### Design

The proposed research is a 6-week open study with follow-up-points at 3 and 12 months from the beginning of the study. The participants will take part in 6 group meetings each lasting 2 hours. The meetings will be supervised by a trained psychologist and a physiotherapist according to a CB intervention model presented by Linton [22]. At the beginning of the study, prior to the randomization, all the patients will participate in groups of about 20 people to hear a lecture regarding the current treatment guidelines for knee OA provided by the study doctors. They will also receive the patient-version booklet of the Finnish Current Care (CC) guideline on knee and hip OA [26]. The study protocol does not interfere with the usual care that the participants may receive from their general practitioner (GP) in primary health care during the study period. Questionnaires will be sent to all participants at the beginning of the study and at two follow-up points (3 and 12 months). The inclusion and exclusion criteria for the study patients are listed in Table 1. The study design is illustrated in Figure 1.

**Figure 1 F1:**
[figure not shown]
**The study design.** GP = general practitioner; CB = cognitive-behavioral; WOMAC = Western Ontario and McMaster Osteoarthritis Index; RAND-36 = the RAND 36-item health survey; 15D = generic 15D instrument; BDI-21 = 21-item Beck Depression Inventory; BAI = Beck Anxiety Index; TSK = Tampa Scale for Kinesiophobia; PCS = Pain Catastrophizing Scale; PSEQ = Pain Self-Efficacy Questionnaire; LS = life satisfaction; SOC = sense of coherence; GAC = global assessment of change.

**Table 1 T1:** Inclusion and exclusion criteria

**Inclusion criteria:**	
1.	Age 35–75 years
2.	Pain within the last year in or around the knee occurring on most days for at least a month [27]
3.	Knee pain greater than or equal to 40 mm on a 100-mm visual analogue scale (VAS) in the WOMAC* [28-31] pain subscale for one week prior to study entry
4.	KL** 2–4 [32] radiographic knee osteoarthritis
5.	Able to attend 6 intervention sessions
**Exclusion criteria:**	
1.	Severe psychiatric or psychological disorder***
2.	Other back or lower limb pain symptoms more aggravating than knee pain
3.	Previous or planned lower extremity joint surgery
4.	Inability to complete the study ****

*Western Ontario and McMaster Universities Osteoarthritis Index.

**Kellgren–Lawrence radiologic score for knee osteoarthritis.

***Psychotic illnesses or psychological disorders that had led to hospitalization or disability to work.

**** Inability to fill in the questionnaires or uncertainty in ability to complete the study due to possible changes in the near future related to health, family, or living conditions.

### Participants and recruitment

Our aim is to recruit 108 patients mainly from primary care providers in the Kuopio area of eastern Finland. Our primary recruitment strategy is to dispatch recruitment letters to patients aged from 35 to 75 years who have had knee radiographs with knee OA changes taken in public primary care locations (Kuopio Health Centre or Kallaveden Työterveys). The study doctors will check the knee radiographs of each patient from an X-ray database and knee radiographs will be graded according to the Kellgren-Lawrence (KL) classification [32]. The recruitment letter will be sent to those subjects with KL grade ≥2, which has been used as a cut-off to classify knee OA [33]. In conjunction with this recruitment strategy, advertisements requesting potential study candidates to contact the study doctors will be placed in the facilities of local primary care providers as well as in the outpatient clinics of the Department of Orthopedics and the Department of Physical and Rehabilitation Medicine at Kuopio University Hospital. Physicians and surgeons working at these locations will also be informed about the study and asked to distribute the advertisements to patients with knee OA.

All study candidates will receive a recruitment letter containing information about the study as well as a preliminary questionnaire and an informed consent form. The preliminary questionnaire will contain a comprehensive list of other comorbidities, including psychiatric illnesses. In the preliminary questionnaire the patients will be asked if they have other back or lower limb pain symptoms that are more aggravating than their knee pain (yes/no). After receiving the signed informed consent and the questionnaire, the study doctors will check the knee radiographs based on KL classification and determine the patient’s eligibility according to the inclusion and exclusion criteria of the study (Table 1). Potential study patients will be able to contact the study doctors by phone or email throughout the recruitment process with any questions concerning the trial.

The patients will be randomly assigned to either the GP care and intervention group (n = 54) or the GP care control group (n = 54). Randomization will be conducted in blocks of six, separately for men and women. A computer-generated code for randomization will be constructed by a statistician who will not meet the study patients, and it will be administered via sealed opaque envelopes. The personnel responsible for data collection will be blinded to group assignment and will not be involved in providing the interventions. The code for randomization will be opened only after the statistical analyses have been performed after the 12-month follow-up point.

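### A single published block size of six within each sex could make up to a quarter of allocations foreseeable in the worst case; varying the blocks and opening envelopes by lecture group would remove most of that

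*Protocol article*

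**What the plan says.** The section Participants and recruitment fixes the scheme: "Randomization will be conducted in blocks of six, separately for men and women", with equal arms of 54. The list is "constructed by a statistician who will not meet the study patients, and it will be administered via sealed opaque envelopes". On blinding, the same section says: "The personnel responsible for data collection will be blinded to group assignment and will not be involved in providing the interventions". The study doctors, after receiving signed consent and a preliminary questionnaire, "determine the patient’s eligibility according to the inclusion and exclusion criteria of the study".

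The Design section opens with "The proposed research is a 6-week open study". It adds that all patients hear a lecture in groups of about 20 before they are randomized. The Intervention section has the treated arm meet weekly in groups of 8–10.

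One exclusion in Table 1, inability to complete the study, is explained partly as "uncertainty in ability to complete the study due to possible changes in the near future related to health, family, or living conditions".

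**The concern.** Sealed opaque envelopes hide the list, but they do not prevent deduction. When every block has the same known length, a person who has seen the earlier allocations in a stratum can tell when one arm is full and what the rest of the block must be. Here there are only two strata, men and women, and attendance at the group sessions makes allocation visible afterwards. The eligibility decision includes a criterion that calls for judgement about whether a person will complete the study.

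If the person applying that criterion could foresee the next allocation, likely attenders could be steered towards the intervention arm. The primary outcome is self-reported pain, so selection on motivation or expectation could bias it. The planned analysis of change from baseline would deal with selection on measured baseline pain, but not with selection on unmeasured traits.

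**Working it through.** The article gives no figure for predictability, so there is none to reproduce.

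**Inputs from the article.** Block size 6; ratio 1:1, so 3:3 within a block; two strata; 54 + 54 = 108 patients; lecture groups of about 20.

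**Assumptions.** The observer knows the block size, where each block starts and every earlier allocation in that sex. The share of women is not given and was varied from 50% to 80%.

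**1. Certain allocations, one patient at a time.** A 3:3 block has C(6,3) = 20 equally likely sequences. The allocations known in advance are the final run of identical assignments:
- final run of 1: 12 sequences, 12 × 1 = 12 certain
- final run of 2: 6 sequences, 6 × 2 = 12 certain
- final run of 3: 2 sequences, 2 × 3 = 6 certain

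The total is 30 of 20 × 6 = 120, or 25%. The closed form agrees: 2m/(m + 1) with m = 3 gives 1.5 per block, and 1.5/6 = 25%. With 18 full blocks that is 27 of 108. Simulating 108 patients in two strata with incomplete last blocks gave 24.0% to 24.1% across the assumed shares of women.

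**2. Best guess.** Always guessing the arm that is behind gives m + (4^m / C(2m,m) − 1)/2 correct per block. For m = 3 this is 3 + (64/20 − 1)/2 = 4.1, and 4.1/6 = 68.3%, against 50% by chance.

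**3. Lecture groups randomized together.** If eligibility for about 20 people is settled before any of them is allocated, only the unfinished part of a block left by the previous group can be foreseen. Suppose a group boundary falls equally often after 0 to 5 places of a block:
- after 0, 1 or 2 places, nothing is certain
- after 3, the last 3 are certain with probability 2/20: 0.3
- after 4, the last 2 are certain with probability 8/20: 0.8
- after 5, the last 1 is always certain: 1.0

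The mean is (0.3 + 0.8 + 1.0)/6 = 0.35 per stratum per boundary. Groups of 20 make five boundaries in 108 patients, so 0.35 × 2 × 5 = 3.5, and 3.5/108 = 3.2%. Simulation gave 3.2% to 3.3%.

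**4. Randomly varying blocks, one patient at a time.** Each size is taken as equally likely, there are 54 patients per stratum, and the observer knows the set of sizes but not their order (simulation):

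| Block sizes | Certain | Best guess correct |
|---|---|---|
| 6 only | 25% | 68% |
| 4 and 6 | 6% | 69% |
| 4, 6 and 8 | 2% | 68% |

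Mixing sizes removes nearly all certainty but does not lower best-guess success.

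**The case against.** A reader might infer that a quarter of allocations are in fact predictable to the study doctors. The article does not support that. It gives them no running record of allocations by sex. The list is made by a statistician without patient contact, data collectors are blinded, and a psychologist and a physiotherapist run the sessions.

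The order of events also works against the worst case. Consent comes before the eligibility decision, and the lecture comes before randomization. A lecture group of about 20 split equally gives about 10 per arm, close to the stated session size of 8–10. That suggests allocation by group, although the article does not say so.

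It is also fair to say that a journal article commonly leaves to the full protocol who opens the envelopes and when, so that silence is not a fault. A fixed block of six is a common choice and contradicts nothing else in the text.

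These arguments reduce the point but do not remove it. The single block size is stated, not omitted. The study doctors are not among those named as blinded. The Discussion has the whole research group present at the lecture, and the section on the intervention describes the two therapists as trained together with the other members of that group. Knowledge of earlier allocations is therefore neither shown nor excluded.

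**Conclusion.** The point stands as a minor design weakness. The stated rule allows up to 25% of allocations (about 24% with incomplete last blocks) to be known before the envelope is opened. This bound rests on three conditions: the study doctors know the block size, they learn earlier allocations by sex, and patients enter one at a time. If each lecture group is randomized together after eligibility is settled, the share is about 3%, and the article's sequence makes that the likelier case.

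Two stronger readings should be avoided. Nothing in the article indicates that allocation was or would be subverted. Nor does printing the block size in the article show that recruiting staff knew it during enrolment.

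**What to change.** Have the independent statistician generate the list with randomly varying block sizes within sex, for example 4, 6 and 8, and keep the sizes from anyone who recruits or judges eligibility. State that envelopes are opened only after eligibility and baseline data are final for the whole lecture group. The first step deals with certain allocations. The second is needed because mixed blocks leave best-guess success at about 68%.

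If allocation by lecture group is already intended, one sentence saying so resolves most of the concern. Regenerating the list takes minutes. The cost is a slightly larger chance imbalance in arm sizes.

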### Intervention

A CB group intervention with 6 weekly sessions will be supervised by an experienced psychologist and a physiotherapist. The sessions will take place in a group of 8–10 persons according to the model presented by Linton [22]. Each session will last for 2 hours with a 15–20-minute break to enhance peer support and social bonding. The outline of the sessions will include an introduction (15 min), lecture (knowledge and insight, max 15 min), problem solving (in pairs/teams, 15–20 min), skills training (15–20 min), homework assignments (15 min) and a résumé (feedback) of the session (15 min). A patient example of a knee OA pain patient will be used throughout the intervention as a basis for discussion and practice in problem solving. An outline of each session is presented in Table 2. The psychologist is the principal leader of the CB intervention. The physiotherapist’s tasks are to lead the relaxation exercises, provide the information of OA pain mechanisms in the first session, offer advice about suitable exercises in the second session, and facilitate the group in general when needed. Both the intervention and the control group will continue side by side with the usual GP care that patients may receive in the primary care throughout the study.

**Table 2 T2:** **An overview of the content of the cognitive-behavioral intervention based on Linton (2005) **[22]

**Session**	**Focus**	**Skills**	**Objectives**
1	Causes of pain and the prevention of chronic problems	Problem solving	•To provide information about the causes of pain.
		Applied relaxation	•To provide information about the risk of chronic pain problems.
		Learning and pain	•To help participants in identifying relevant factors in one’s own pain problem.
			•To train problem-solving and relaxation skills.
			•To teach pain control techniques.
2	Managing your pain	Activities, maintain daily routines	•To provide information about the relationship between activity and musculoskeletal pain.
			Scheduling activities	
		Relaxation training	•To help participants in understanding fear avoidance behavior.	
			•To teach participants to identify goals for a satisfying activity level.	
			•To teach management skills: scheduling, pacing, graded increase.	
			•To teach cognitive skills to minimize problems with activities.	
			•To introduce stress and stress management.	
3	Promoting good health, controlling stress at home and at work	Warning signals	•To provide information how pain problems may be prevented.	
		Cognitive appraisal	•To provide information how to utilize thoughts and behaviors in preventive efforts.	
		Beliefs	•To teach how to apply various skills (relaxation, activity management, beliefs, pauses etc.) as coping.	
			•To help the participants to identify targets for developing coping strategies.	
			•To teach applied relaxation as coping strategies.	
4	Adapting for leisure and work	Communication skills	•To provide opportunities to receive reinforcement for correct ”coping” approximations from the group.	
		Assertiveness		
		Risk situations	•To provide information about how workplace and family may be influenced by the participant’s pain problem.	
		Applying relaxation		
			•To provide information and coping strategies concerning situations where the workplace and family may influence the participant’s pain perceptions.	
			•To teach assertiveness in using the coping skills learnt.	
			•To help participants to identify supportive behaviors from others.	
			•To teach participants to prompt these behaviors to promote positive relationships with family and friends.	
			•To teach how to apply rapid relaxation to risk situations.	
			•To teach participants how to employ several coping techniques in social situations.	
			•To begin to plan a personal coping program.	
5	Controlling flare-ups	Plan for coping and flare-ups	•To provide information about flare-ups and maintenance.	
		Coping skills review	•To teach how to use applied relaxation as coping.	
		Applied relaxation	•To teach how to apply their skills to cope with flare-ups.	
		Own program	•To develop a personalized coping program.	
			•To develop a self-care strategy that may reduce the need for healthcare visits.	
6	Maintaining and improving results	Risk analysis	•To reinforce appropriate coping behaviors.	
		Plan for adherence	•To provide information about maintenance and adherence.	
		Own program finalized	•To teach participants to do risk analysis and enhance adherence.	
			•To teach participants about enhancing and fine-tuning their program.	
			•To evaluate the course and participants’ progress.	

The same psychologist and physiotherapist who are both experienced in group-based rehabilitation interventions as well as in pain management will arrange the CB program for all the intervention groups. They have been trained for this particular CB intervention by going through in detail the session manual for therapists [22] and its Finnish translated version together with the other members of the research group.

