### Statistical analysis

The mean (±SD) knee joint pain score (WOMAC, VAS) was estimated by using the results of the knee joint pain scores in previous studies [60,61]. Since the knee pain has to be ≥40 mm on a 100-mm VAS (WOMAC) in this present study, we postulated that there will be a mean of at least 48±16.2 mm in the WOMAC pain subscale at baseline. In our study the 20% reduction in primary outcome (WOMAC pain) due to the intervention was considered as being clinically relevant in accordance with the OMERACT-OARSI set of responder criteria [62]. In the comparison of the mean pain scores between the groups, 54 patients per group are needed according to a power calculation with the two-tailed Student t-test with a 5% significance level and 80% power, assuming a 20% dropout rate [63].

Demographic characteristics and baseline data will be summarized by descriptive statistics. Randomly missing data in the longitudinal set-up will be imputed using expectation–maximization algorithm before the analysis in order to follow the intention to treat principle. Data on various psychological variables predicting reported knee pain will be assessed by multiple regression analysis. For outcomes measured on a continuous scale, differences between groups in the mean change from the baseline to 12 months will be evaluated using the linear mixed modeling. The model assumptions will be checked by standard diagnostic plots. The participant rating of the global assessment of change will be compared between the two groups using the two-tailed Student t-test.

Cost-effectiveness of the intervention will be evaluated by cost-utility analysis which is a techniques that incorporates the expenses of the intervention as well as the costs of the use of health care services and pain medication, sick leaves, rehabilitation and pensions. Utility analysis is based on measurement of QALY from 15D [58]. Life expectancy with 0%, 3% and 5% discounting will be incorporated in the analysis. The cost-effectiveness of the intervention can be evaluated by dividing the overall costs with the QALY.

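### Six or so therapy groups in one arm only: the sample size and the test of the global assessment assume independent patients, and the blinding rule conflicts with a therapy-group term in the primary model

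*Protocol article*

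**What the plan says.** Patients are randomized individually, 54 to each arm (Participants and recruitment). Only the intervention arm is treated in groups: "The sessions will take place in a group of 8–10 persons". Interaction within a group is part of the treatment. Each session has time set aside "with a 15–20-minute break to enhance peer support and social bonding", problem solving is done in pairs or teams, and Table 2 lists reinforcement from the group among the aims of session 4. The same psychologist and physiotherapist lead every group. Controls continue with GP care and are not grouped.

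The Statistical analysis section states "54 patients per group are needed according to a power calculation with the two-tailed Student t-test with a 5% significance level and 80% power", with a 20% dropout allowance. It names no ICC and no design effect. Continuous outcomes, including the primary one (WOMAC pain at 12 months), are to be compared by linear mixed modelling, with no random effects described. The global assessment of change is to be compared by a two-tailed Student t-test.

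On blinding, Participants and recruitment states: "The code for randomization will be opened only after the statistical analyses have been performed after the 12-month follow-up point".

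**The concern.** This is a partially nested design. Patients who work through six sessions together may end up with correlated outcomes, while controls remain independent of one another. If so, the variance of the intervention mean is larger than an independent-patient formula allows. Three consequences follow.

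- The stated power is too high for any positive ICC.
- A plain t-test, as named for the global assessment, rejects a true null hypothesis more often than 5% of the time.
- The primary mixed model is exposed to the same error if it has no therapy-group term. Such a term exists in one arm only, so entering it shows the analyst which arm is which. The rule on opening the code therefore works against the model that the design calls for.

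The error favours declaring a benefit, and the authors hope that the results will bear on care recommendations.

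**Working it through.** **Inputs from the Statistical analysis section.** Baseline mean 48 mm and SD 16.2 mm; relevant difference 20% of 48 = 9.6 mm; two-sided 5% level; 80% power; 20% dropout.

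**Reproducing the plan's figure.** n per arm = 2 × [(1.960 + 0.842) × 16.2 / 9.6]² = 44.7, so 45 evaluable. Then 45 × 1.2 = 54, which is the stated number. Division by 0.8 would give 57. The stated 54 therefore comes from independent patients, with dropout added as a multiplier and no design effect.

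**Number of groups.** 54/10 = 5.4 and 54/8 = 6.75, so about six.

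**Evaluable patients.** 54 × 0.8 = 43.2. I take 43 controls and, in the intervention arm, six groups of 7 (42 patients).

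**Assumption.** The documents give no ICC, so I show 0.01 to 0.10. The total SD is 16.2 mm in both arms.

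**Formulas.**
- Design effect in the intervention arm: DE = 1 + (7 − 1) × ICC.
- True SE = 16.2 × √(DE/42 + 1/43); SE under independence = 16.2 × √(1/42 + 1/43) = 3.515 mm.
- Type I error of the unadjusted test = 2 × [1 − Φ(1.96 × 3.515 / true SE)].
- Valid test: mean of the six group means against the control mean, with Satterthwaite degrees of freedom. Power at 9.6 mm is from simulation; a non-central t approximation agrees within about one percentage point.

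| Assumed ICC | DE | True SE (mm) | Type I error, unadjusted | Approx. df | Power, group-level test |
|---|---|---|---|---|---|
| 0 | 1.00 | 3.515 | 5.0% | 17.5 | 73% |
| 0.01 | 1.06 | 3.567 | 5.3% | 16.8 | 71% |
| 0.02 | 1.12 | 3.620 | 5.7% | 16.1 | 69% |
| 0.05 | 1.30 | 3.772 | 6.8% | 14.4 | 66% |
| 0.10 | 1.60 | 4.013 | 8.6% | 12.4 | 60% |

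Simulating the unadjusted t-test in the same setting gives type I errors of about 5.2% at ICC 0.01 and about 8.5% to 8.7% at ICC 0.10, which agrees with the formula.

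**Separating the causes of the shortfall from 80%.**
1. Dropout inflation: an exact t-test has 79.4% power with 45 per arm and about 77% with 42–43, at ICC 0.
2. Few groups: the group-level test at ICC 0 has 73%, a further loss of about 4 points from the low degrees of freedom.
3. Clustering itself: from 73% to 71% at ICC 0.01 and to 60% at ICC 0.10, a loss of about 2 to 13 points.

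**The case against.** The strongest reply concerns the primary outcome. A linear mixed model is the usual vehicle for a therapy-group effect. The article condenses a fuller plan that is not shown, and the random effects may be set out there. A reader might infer that every planned test ignores the grouping and that the primary type I error exceeds 5%. The documents do not support that: the term is neither stated nor excluded. This part of the reply stands.

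A reader might also infer that the blinding rule makes a therapy-group term impossible. That too goes further than the text, which says when the code is opened, not which variables the dataset holds. What remains is a conflict between two procedures. A group identifier that is present in one arm only reveals the allocation even when its labels are masked, so the rule needs rewording if the term is to be used.

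Third, the ICC may be small. The same two leaders run every group from one manual, which removes between-therapist variance, and the endpoint is self-reported pain at 12 months, long after the six weekly sessions. At ICC 0.01–0.02 the excess type I error is below one percentage point. This is fair as to size. It does not remove variation between groups that arises from their members, and the documents give no basis for taking the ICC as zero.

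Finally, the article does not say that group membership is closed. The sequential six-session programme suggests it, and I rely only on patients being treated together.

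**Conclusion.** The point holds in two places as written. The sample size is an independent-patient calculation for a design with about six therapy groups in one arm, and the Student t-test for the global assessment ignores the grouping. For the primary outcome, inflated type I error is a conditional risk: it requires that the therapy-group term be left out and that the ICC exceed zero. What is established there is the conflict between that term and the rule on opening the code.

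The size rests on the assumed ICC, on equal total variance in the two arms, and on six groups of 7 against 43 controls. The distortion is slight at 0.01–0.02 and material from about 0.05. It would be wrong to put the whole fall from 80% to 60–71% down to clustering, because the dropout inflation and the few degrees of freedom already bring it to 73%.

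This should be fixed before analysis. It does not undermine the trial as designed.

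**What to change.** 1. Record each intervention patient's therapy group.
2. Specify the primary model as partially nested: a random therapy-group effect in the intervention arm only, residual variance by arm, and Satterthwaite or Kenward-Roger degrees of freedom. If a plan not shown already does this, the article need only say so.
3. Analyse the global assessment of change in the same way, in place of the plain t-test.
4. Amend the rule on the randomization code so that the analysis program is locked before unblinding and run once group membership is released. The analysis choices then remain blinded.
5. Restate the power at N = 108 over a stated ICC range, with the effect of dropout shown separately.

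The cost is some wording and one variable that the group leaders already know. No extra patients are needed. The downside is fewer degrees of freedom and a stated power below 80%.
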